The Chinese Cardiovascular Association launched the National Chest Pain Center Accreditation Program (CHANGE) in January 2016. This is the first nationwide, hospital-based, multifaceted, continuous quality improvement (QI) initiative, with aims to monitor and improve the quality of care for acute cardiac events (ClinicalTrials.gov, NCT04014972). The QI initiatives, as implementation strategies, include a bundle of evidence-based interventions adapted for implementation in China. These are in line with global best practices: (i) accreditation of hospital-based chest pain centers (CPCs), (ii) establishing a unified data registry for quality monitoring and assessment, and (iii) providing ongoing quality review and feedback. The operational structure was developed at the start of the program (Appendix Figure 1). The program is made available to all secondary and tertiary hospitals, and hospitals continue to join the program in a staggered manner. With the support of the National Health Commission (NHC), based on the CPC Accreditation Criteria issued by the Chinese Society of Cardiology, the CHANGE program has implemented the accreditation and development of CPCs (Appendix Figure 2). The CHANGE program developed the China CPC Data Reporting Platform, a web-based, unified national database serving as a national surveillance system for monitoring, evaluation, and feedback regarding quality of care for reported STEMI events (Appendix Table 1). As of June 30, 2019, there were 2,885 hospitals across 31 provinces of China and a total of 463,827 patients with a STEMI diagnosis enrolled in the program. Our preliminary analysis using baseline and quarterly data during January 2016 and June 2019 demonstrated that the QI initiatives can shorten onset to reperfusion times and subsequently reduce in-hospital mortality.

Challenges to quality improvement initiatives in response to COVID-19

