(2) Quality monitor and assessment	▪ Accredited hospitals should continuously report data for monitoring and feedback. ▪ The indicators for measuring the CPC performance in the quarterly and annually benchmarked reports are developed by the China CPC Headquarters, based on the ACC/AHA Performance Measures and clinical practice guidelines. ▪ There are two sets of performance measures respectively for comprehensive and basic CPCs. ▪ Ranking of a CPC is calculated based on the percentile of each indicator and a weighted composite score. The score of 100, 80, 60, 40, 20, and 0 are for ranking the top 10%, 10–30%, 30–50%, 50–70%, 70–90%, and 90–100% of the measure among the entire accredited CPCs.	Current and optimized
(3) Quality review and feedback	▪ Improvement in adherence to the guideline recommendations is facilitated through monthly and quarterly hospital-specific performance feedback reports. ▪ The hospital-specific data are compared against a variety of internal and external benchmarks, including the temporal trend in performance and comparison points to regional or national performance thresholds. ▪ A series of regular meeting, QI analysis meeting, and case study meeting are carried out at least once every quarter for sharing of ‘best practice’ clinical support tools.	Current and optimized
(4) Dedicated regional coordinator	▪ Dedicated regional coordinator charged with implementing systematic improvements within every hospital and EMS agency will be assigned by city-level CPC Alliances. ▪ Dedicated regional coordinators will work with the local health bureau to promote the optimized QI initiatives. ▪ The work of dedicated regional coordinators will include synthesizing emergency infection protocols to contain COVID-19 with QI initiatives, coordinating care between community, hospitals, and EMS agency, maintaining the safety of healthcare workers, minimizing contamination of laboratory facilities. ▪ The work of dedicated regional coordinators will be supervised by the city-level CPC Alliances and the China CPC Headquarters.	Optimized
(5) Education and training activities	▪ The training on emergency infection protocols instituted in hospitals to contain COVID-19 targeting at healthcare professionals will be conducted by hospitals ▪ Education on STEMI awareness and COVID-19 knowledge targeting community residents will be conducted by community health centers, which are trained and supervised by hospitals within the medical consortium.	Optimized

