*QI* Quality improvement; *CHANGE* National Chest Pain Center Accreditation Program; *CPC* Chest pain center; *EMS* Emergency medical services; *ACC/AHA* American College of Cardiology/American Heart Association; *COVID-19* Coronavirus disease 2019; *STEMI* ST segment elevation myocardial infarction

Sampling

In this study, we will conduct a rollout to registered hospitals every 3 months, which will be based on the pilot experience, local contextual factors, budgetary and feasibility considerations. Patients with STEMI in registered hospitals will be consecutively enrolled in five 3-month steps. No intervention will be applied in the first step among all registered hospitals. Hospitals will be randomly allocated to one of four clusters, with six hospitals in each cluster. Each cluster will commence the intervention at one of the four remaining steps. All hospitals will be on the intervention in the final step. Characteristics of hospitals with STEMI cases enrolled during January and June 2020 are shown in Table 2, by district (Table 2).

**Table 2 Tab2:** Characteristics of sample hospitals, by district

City	District	Population	Land area (km^2^)	Number of hospitals	STEMI patients	In-hospital mortality
Wuhan	Jianghan	496,289	28.3	3	459	1.53
	Qiaoko	528,604	40.1	4	319	3.13
Suzhou	Gusu	957,500	83.4	4	167	3.86
	Kunshan	1,665,900	931.5	6	157	1.27
Shenzhen	Futian	1,633,700	78.5	4	250	6.00
	Luohu	1,039,900	78.7	3	229	4.37

*STEMI* ST segment elevation myocardial infarction

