### Statistical methods

Task 1. Design of the optimized QI initiatives

For Task 1, the analytic hierarchy process will be applied to identify the priority intervention areas in the quality-of-care response to COVID-19. A facilitated and structured interview matrix technique will be used to analyze the interview results for organizational analysis and strategic planning of priority settings. The structured interview matrix will follow a graded approach to collaboration involving discussion at three levels, using a three-step process: (1) interviews conducted by participants in the group; (2) small group deliberation; and (3) a facilitated, plenary discussion with the full group.
(2)Task 2. Implementation and evaluation of the optimized QI initiatives(3)To investigate the effectiveness of the optimized QI initiatives with respect to quality metrics of STEMI care in response to COVID-19

Primary analysis will be performed according to the intention-to-treat principle. All analyses of outcomes will be at the individual level but will account for the clustering of patients at the hospital level. Comparisons of quality metrics between intervention and control participants will be conducted using the *t*-test and *χ*^2^ test. To analyze intervention effects, generalized estimating equation models will be used to account for the clustering within hospitals. The primary model will include a fixed effect for time and a binary variable for the effect of the intervention. The intervention effects will be summarized as the resulting odds ratios and difference of proportions for binary outcomes or mean differences for continuous outcomes. We will also conduct two-level generalized linear mixed models with patient and hospital as the first and second levels, respectively, using covariate-adjusted analyses. The model will also include the severity of the COVID-19 pandemic as a confounding factor. Appendix Table 2 depicts how the results will be displayed.
2)To examine the implementation strategy of the optimized QI initiatives using measures of reach, adoption, implementation, and maintenance in response to COVID-19

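### The primary GEE leaves out each hospital's pre-trial outcome level, which the registry should already hold; adding it is a cheap, modest precision gain, not a correction of an error

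*Protocol article*

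**What the plan says.** Statistical methods (Task 2, effectiveness) makes GEE the main analysis: "generalized estimating equation models will be used to account for the clustering within hospitals". Its content is fixed in the next sentence: "The primary model will include a fixed effect for time and a binary variable for the effect of the intervention". Covariates come in a separate, additional analysis: "We will also conduct two-level generalized linear mixed models with patient and hospital as the first and second levels, respectively, using covariate-adjusted analyses". The only covariate named is pandemic severity ("The model will also include the severity of the COVID-19 pandemic as a confounding factor"). That sentence follows the mixed-model sentence, so it is unclear whether it also applies to the GEE.

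The registry outcomes come from the China CPC Data Reporting Platform, described in the Background as "a web-based, unified national database serving as a national surveillance system for monitoring, evaluation, and feedback regarding quality of care for reported STEMI events". It was in use before the trial. The text on sampling states: "Characteristics of hospitals with STEMI cases enrolled during January and June 2020 are shown in Table 2, by district". No section plans to use these pre-trial values in the primary model.

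**The concern.** A stepped wedge estimate combines comparisons within a hospital over time with comparisons between hospitals in the same quarter. Stable differences between hospitals add noise to the second kind. With six hospitals per sequence and no stratification described, chance imbalance in hospital level between sequences is to be expected.

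There are signs that hospitals differ. In-hospital mortality in Table 2 runs from 1.27% to 6.00% across districts. The programme also separates two levels of centre (Table 1, item 2: "There are two sets of performance measures respectively for comprehensive and basic CPCs"), although the article does not say how the 24 trial hospitals divide between them.

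The number of hospitals is fixed at 24, so further precision has to come largely from the analysis. A pre-trial value of the same outcome is an obvious candidate. It precedes the intervention, so adjusting for it cannot introduce post-treatment bias. At stake is the width of the confidence intervals for PCI rate, EMS share and the time targets.

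**Working it through.** **The plan's own figures.** Table 2 sums to 459 + 319 + 167 + 157 + 250 + 229 = 1,581 patients, the same number as the stated sample size. That sample size does not reproduce: individual randomisation to detect 3.18% against 2.703% (a relative 15% reduction) with 80% power, two-sided, already needs about 39,392 patients. This is a separate matter. It is noted here because 1,581 and the accrual rate give different trial sizes, and both are carried below.

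**District heterogeneity.** Rounded deaths from Table 2 are 7/459, 10/319, 6/167, 2/157, 15/250 and 10/229. Chi-square = 13.6 on 5 df, p = 0.018.

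**Inputs from the article.** 24 hospitals, 4 sequences of 6, 5 periods, ICC 0.005 for mortality. Pre-trial patients per hospital: n = 1,581/24 = 65.9. Accrual at the Table 2 rate: 1,581 × 15/6 = 3,952 patients, or m = 3,952/(24 × 5) = 32.9 per hospital-quarter.

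**Assumptions not in the article.** Process-outcome ICC 0.02–0.20; exchangeable working correlation; correlation ρ of 0.7–1.0 between a hospital's true pre-trial and in-trial level.

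**Formulas.** Scale the total variance to 1, with τ² = ICC and σ² = (1 − ICC)/m. The stepped wedge variance is

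Var = Iσ²(σ² + Tτ²) / [(IU − W)σ² + (U² + ITU − TW − IV)τ²]

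with I = 24, T = 5, U = 60, W = 1,080, V = 180. So IU − W = 360, and the second bracket is 3,600 + 7,200 − 5,400 − 4,320 = 1,080. Adjustment replaces τ² by τ²(1 − ρ² × rel), where rel = n·ICC/(1 + (n − 1)·ICC).

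**Example, ICC 0.05, equal hospitals.** σ² = 0.95/32.94 = 0.02884; rel = 0.776.
- Unadjusted: 24 × 0.02884 × 0.27884 / (10.38 + 54.00) = 0.002998.
- Adjusted, ρ = 1: τ² = 0.01119, Var = 0.002612, ratio 0.871, a saving of 12.9%.
- Adjusted, ρ = 0.8: τ² = 0.02516, Var = 0.002850, ratio 0.951, a saving of 4.9%.

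**Full grid.** Hospital volumes set to the Table 2 district averages, averaged over random allocations; variance saved with about 3,952 patients:

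| ICC | ρ = 1 | ρ = 0.9 | ρ = 0.8 | ρ = 0.7 |
|---|---|---|---|---|
| 0.005 (mortality) | 4.0% | 3.1% | 2.4% | 1.8% |
| 0.02 | 9.8% | 6.8% | 4.7% | 3.3% |
| 0.05 | 12.9% | 7.2% | 4.5% | 3.0% |
| 0.10 | 14.4% | 6.0% | 3.4% | 2.1% |
| 0.20 | 15.2% | 4.1% | 2.1% | 1.2% |

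A logistic GEE simulation for a 60% outcome gave noncentralities of 3.32 unadjusted and 3.53 adjusted at ICC about 0.05, and 2.94 and 3.21 at about 0.20. The savings are 1 − (3.32/3.53)² = 12% and 1 − (2.94/3.21)² = 16%, which sets the upper end of the range.

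**Variations.**
- With 1,581 patients the best case (ICC 0.20, ρ = 1) is about 23%; at ρ = 0.8 the saving is about 4–7%.
- If 20% of the hospital variance changes independently by quarter but the permanent part is identical before and during the trial, the saving is about 11% at ICC 0.05 and 13.5% at 0.20. Adding ρ = 0.8 for the permanent part brings both to about 5%.
- Under an independence working correlation the saving at 3,952 patients is far larger, about 20–91%, because that estimator makes poor use of within-hospital comparisons.

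**The case against.** The strongest reply is that nothing here is wrong. A GEE with time and intervention is a valid stepped wedge analysis, and randomisation protects against systematic imbalance. The first step is a control period in all 24 hospitals, so an exchangeable GEE already has a concurrent baseline for each hospital, which is why the additional gain is small. A covariate-adjusted model is planned as well, and an analysis plan that is not shown may list covariates and the working correlation. All of this stands as a limit on the point. It does not remove it, because the article itself fixes the terms of the primary model and gives covariates to a different one.

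The size is also open to challenge. A reader might take 12–16% as the expected gain. The article gives no process-outcome ICC, no working correlation and no hospital-level stability, and that figure needs hospital levels that hardly shift between the two periods. The Pilot study section reports PCI use falling from 71.3% to 60.1% between 2019 and 2020. That is an overall change which the time terms would absorb; it leaves ρ unknown and does not show it to be low. The only between-hospital variation shown is for mortality by district, and mortality is the outcome that gains least.

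A reader might also infer that the planned estimate is biased, or that adjustment would rescue the power for mortality. Neither follows: chance imbalance is already part of the sampling variance, and 2–4% is trivial against the gap between 1,581 and 39,392.

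**Conclusion.** The point holds as an efficiency improvement. The primary model omits a prognostic, pre-intervention value that the sponsor's own platform should be able to supply. That every process outcome can be extracted by hospital for the pre-trial months is inferred from the platform's role; Table 2 prints only patient numbers and mortality.

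The gain was positive in every scenario examined. For process outcomes it is about 1–16% of the variance with an exchangeable correlation and Table 2 accrual, and about 1–7% if the pre-trial/in-trial correlation is 0.7–0.9. For mortality it is about 2–4%. The ICCs for process outcomes, the correlation ρ and the working correlation are assumptions.

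**What to change.** In the primary GEE for each registry outcome, prespecify:
- the hospital's own value of that outcome over the last 6 months before step 1;
- patient age and sex.

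Keep hospital-level covariates few, because there are only 24 hospitals; chest pain centre level (comprehensive or basic) is optional. Exclude anything the intervention can change, such as arrival mode or delay. Fix the list before outcome data are examined, and keep the time-and-intervention model as a sensitivity analysis.

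The cost is a few lines of analysis-plan wording and one extract from the platform. There are two downsides. The odds ratio becomes conditional on the covariates, so report the difference of proportions, already a planned summary, in standardised form beside it. About one hospital-level degree of freedom is lost for each hospital-level covariate. The 1-year outcomes come from the telephone survey and are not covered by this change.

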## Discussion

The COVID-19 pandemic compromises the quality of care for the acute cardiac events. How to minimize the untoward impact of the evolving COVID-19 pandemic on the health care quality has been an imminent agenda for policymakers as well as researchers. This project will be the first to develop and implement hospital-based interventions that improve the quality of care for acute cardiac events in response to COVID-19, and to develop strategic options in scale-up activities for the quality improvement initiatives in response to COVID-19 and other potential pandemics or health emergencies. We have described our rationale, study design, and implementation strategy details regarding this stepped wedge cluster randomized control design.

### Feasibility of the project

With the support of the NHC, the project will be conducted in collaboration with the Peking University First Hospital and the Chinese Cardiovascular Association, which is committed to organizing and implementing the CHANGE program. Supervised by the Chinese Cardiovascular Association, the provincial- and city-level CPC Alliances manage and undertake implementation of the optimized QI initiatives at provincial and city levels, respectively. Data for hospital-based assessment will be collected via the China CPC Data Reporting Platform, which is managed by the Chinese Cardiovascular Association. Necessary personnel, including the project promotor, and dedicated regional coordinators in every hospital and EMS unit, will be assigned by the city-level CPC Alliances. The local project office in each district will be set up to manage personnel, information, and institutional coordination. The project promotor in each district will work with the local health bureau to promote implementation of the optimized QI initiatives, and they will be supervised by the city-level CPC Alliances.

Four specific activities will be conducted to mitigate potential risk during all procedures of this project, through effective technical and financial management and to coordinate collaborative functions. First, we will develop effective coordination mechanisms at all stages, to achieve the project objectives and maintain communication between project partners. Second, we will ensure the overall administrative, legal, and financial management of the project, and each participant will have their own responsibility with regard to these areas. Third, documentation and reporting of the project activities, workshop results, preparation of guides, and progress/review reports will be included, to resolve unforeseeable issues that may occur during the project. Fourth, we should ensure that ethical issues are appropriately taken into account and in a timely manner; and administrative permissions should be obtained that are needed to start and maintain the project activities.

Monitoring of the research process will be conducted according to the tasks and approaches. The activities of monitoring are shown in the flowchart (Appendix Table 4). Quality control procedures will be carried out, to help implement the activities through effective technical and financial management. The plan for quality control procedures according to approaches and the potential risks is shown below (Appendix Table 5).

### Pilot study

We have performed a retrospective cohort study drawing on unified registered-hospital report data from the CHANGE program. We investigated the effectiveness of the current QI initiatives in terms of quality metrics of STEMI care during January 2020 and June 2020 by comparing the data at baseline and in the final quarter. We then compared changes in the quality metrics of STEMI care between January and June 2019 and between January and June 2020 using difference-in-difference analysis.

The primary results of the polit study are as follows. First, baseline and quarterly data during January 2016 and June 2019 demonstrated that implementing the current QI initiatives significantly improved many process indicators. For example, the onset-to-device time decreased from 291 minutes to 233 minutes, and the percentage of cases with FMC-to-device time≤ 90 minutes increased from 43.0% to 54.1% between baseline and the final quarter. Second, during January and July 2020, admissions of patients with STEMI decreased by 42%, compared with the same period in 2019. Baseline and quarterly data showed that door-to-balloon and the FMC-to-device median (q1, q3) time increased from 17.5 (10.0, 46.0) and 52.0 (12.0, 86.0) minutes to 34.0 (15.0, 48.0) and 63.0 (15.0, 94.0) minutes, respectively (*p* = 0.001, *p* = 0.005). The onset-to-FMC time accounted for more than 70% of the total delayed time. Third, compared with January to June 2019, many process indicators deteriorated from January to June 2020. For example, the proportion of patients admitted via EMS was only 4.2% in 2020, much lower than that in 2019 (9.3%, *p* = 0.013), and rate of PCI practice declined from 71.3% to 60.1% (*p* = 0.002).

The additional expected primary results of the pilot study will include the following: First, the CFIR framework will be developed to support evaluation of implementation of the current QI initiatives within the context of COVID-19, and to produce actionable evaluation findings intended to improve implementation in a timely manner; Second, In-depth interviews with key informants will be conducted to identify barriers and facilitators to implementation of the current QI initiatives that may emerge in the context of COVID-19, using the CFIR framework to guide data collection, coding, analysis, and reporting of actionable findings for the design of the optimized QI initiatives.

### Strengths and limitations

This study will provide contributions to the literature as follows. First, this study will take lead to identify multilevel factors that emerge within the context of COVID-19 and influence implementation of the interventions to improve the quality of care for acute cardiac events, using the CFIR framework. The findings will provide implications for where adjustments to the interventions could be made in response to COVID-19 and other potential pandemics or health emergencies. Second, the study design will provide a novel model to measure complex interventions in real-world health care system settings, including measures of clinical effectiveness and implementation strategies for quality improvement initiatives of acute cardiac care in response to COVID-19, by using a stepped wedge cluster randomized control design under an implementation science framework, the RE-AIM model. Third, the outcomes of this study will generate actionable knowledge about process outcomes and feasibility, including core components that are transferrable, and where local adaptation is needed for scale-up activities in low- and middle-income settings, to improve the quality of care for acute cardiac events in response to COVID-19 and other potential pandemics or health emergencies.

However, this project has at least two limitations. First, in a real-world pragmatic stepped wedge trial, there will be concerns related to confounding, bias, and temporal trends that may limit the validity of the findings. However, we will use a cluster randomized control design, which is widely considered the best design for causal inference. The pragmatic design will be chosen because it allows iterative dissemination of results internally, to support programmatic improvements; it is anticipated that the project will be beneficial and receipt of the intervention is the strong preference of all registered hospitals. Nevertheless, we will use a modest effect size, cluster randomization, and an analysis plan to mitigate these limitations.

Second, the voluntary participation of hospitals limits our generalization to hospitals not participating in this registry, although hospital recruitment remains ongoing. Willingness of enrolled hospitals to participate in the program may indicate a greater focus on quality improvements and thus may limit reproducibility at other hospitals. We investigated the clinical regulation rules in the sample hospitals and hospitals that have not participated in the program; we found that differences in the clinical pathways and health resource mobilization were not significant. One explanation for this is that most hospitals in China are public and follow similar regulations issued by the NHC. Nevertheless, we will minimize the limitations at baseline through site selection and randomization.

